**Effect of combined exercise training on inflammatory factors and levels of hormones associated with blood glucose homeostasis in pediatric type 1 diabetes**

**Protocol summary**

Study aim

Effect of combined exercise training on inflammatory factors and levels of hormones associated with blood glucose homeostasis in pediatric type 1 diabetes

Design

In this research, 44 children with type 1 diabetes referring to 17 Shahrivar pediatric hospital were randomly assigned in the two groups. They will be divided into two groups; 22 people in experimental and 22 people in control group.

Settings and conduct

The present study is a semi-experimental study among the child with type 1 diabetes of city of Rasht for 16 weeks. Blood sampling is performed after 12 hours of fasting and before and after 16 weeks of concurrent training.

Participants/Inclusion and exclusion criteria

Inclusion criteria: Having age ranges of 8-15 years, A1c≥7, Pediatric type 1 diabetes, No regular exercise Exclusion criteria: more than three session absence from the training

Intervention groups

Intervention group: Combined training group. Aerobic training: sixteen weeks, three times per week. Aerobic exercises were performed with an intensity of 50-75% of maximum heart rate, pilates exercises, 3 set, 6-12 repeat and training using body weight with 20 minutes. Control group: Without intervention

Main outcome variables

IL-1B, HS-CRP, IGF-1, Grows hormone, Cortisol, HbA1c, FBS, CBC

**General information**

Reason for update

Acronym

IRCT registration information

IRCT registration number: **IRCT20150531022498N30**

Registration date: **2019-07-26, 1398/05/04**

Registration timing: **retrospective**

Last update: **2019-07-26, 1398/05/04**

Update count: **0**

Registration date

2019-07-26, 1398/05/04

Registrant information

**Recruitment complete**

Funding source

Expected recruitment start date

2019-02-09, 1397/11/20

Expected recruitment end date

2019-07-22, 1398/04/31

Actual recruitment start date

empty

Actual recruitment end date

empty

Trial completion date

empty

Scientific title

Effect of combined exercise training on inflammatory factors and levels of hormones associated with blood glucose homeostasis in pediatric type 1 diabetes

Public title

Effect of combined exercise training in pediatric type 1 diabetes

Purpose

Prevention

Inclusion/Exclusion criteria

**Inclusion criteria:**

Having age ranges of 8-15 years A1c≥7 Pediatric type 1 diabetes No regular exercise

**Exclusion criteria:**

More than three session absence from the training

Age

From **8 years** old to **15 years** old

Gender

Both

Phase

N/A

Groups that have been masked

*No information*

Sample size

Target sample size: **44**

Randomization (investigator's opinion)

Randomized

Randomization description

Subjects were divided into 2 groups (one control group and one experimental groups) using the simple random method. This sampling will be done based on the red and blue balls inside the box that are randomly taken by the subjects (Red Orb and the Blue Orb of the experimental group).

Blinding (investigator's opinion)

Not blinded

Blinding description

Placebo

Not used

Assignment

Parallel

Other design features

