**Primary outcomes**

**1**

Description

IL-1B

Timepoint

Before and after the end of interventions

Method of measurement

using ELISA Kit

**2**

Description

High-sensitivity C-reactive Protein (hs-CRP)

Timepoint

Before and after the end of interventions

Method of measurement

using ELISA Kit

**3**

Description

IGF-1

Timepoint

Before and after the end of interventions

Method of measurement

using ELISA Kit

**4**

Description

Growth hormone

Timepoint

Before and after the end of interventions

Method of measurement

using ELISA Kit

**5**

Description

Cortisol

Timepoint

Before and after the end of interventions

Method of measurement

using ELISA Kit

**6**

Description

HbA1c

Timepoint

Before and after the end of interventions

Method of measurement

using ELISA Kit

**7**

Description

Fast blood sugar

Timepoint

Before and after the end of interventions

Method of measurement

using ELISA Kit

**8**

Description

Complete Blood Count (CBC)

Timepoint

Before and after the end of interventions

Method of measurement

using ELISA Kit

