**Intervention groups**

**1**

Description

Intervention group: Combined training group. Aerobic training: sixteen weeks, three times per week . Aerobic exercises were performed with an intensity of 50-75% of maximum heart rate ,pilates exercises, 3 set, 6-12 repeat and training using body weight with 20 minuets.

Category

Lifestyle

**2**

Description

Control group: Without intervention

Category

Lifestyle

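### The only exclusion criterion, more than three missed training sessions, can act only after randomisation and only in the training arm, so it opens the comparison to selection bias.

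*Protocol*

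**What the plan says.** The rule appears twice in the protocol, and each time it is the only exclusion criterion. The Exclusion criteria entry reads "More than three session absence from the training", and the Protocol summary has "Exclusion criteria: more than three session absence from the training".

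Under Intervention groups, training is scheduled "sixteen weeks, three times per week" in the experimental arm; the other arm is "Control group: Without intervention". On allocation the protocol says "Subjects were divided into 2 groups (one control group and one experimental groups) using the simple random method", carried out by each child drawing a coloured ball. The planned split is "22 people in experimental and 22 people in control group", and the trial is not blinded. Every primary and secondary outcome is timed "Before and after the end of interventions".

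The protocol does not say what happens to a child who exceeds three absences, sets no counterpart rule for controls, and states no allowance for losses in the 44.

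**The concern.** An exclusion criterion should be decidable before allocation and should apply equally to both arms. This one meets neither condition. A child's absences are observed during the 16 weeks after the ball is drawn, and a control child has no session to miss.

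Attendance is likely to track motivation, insulin adherence, intercurrent illness and family support. Those same traits plausibly affect HbA1c, fasting glucose, hs-CRP and quality of life. If children with poor attendance leave the training arm while their counterparts stay among the controls, the arms differ at the end for reasons other than training. For these four outcomes the distortion plausibly favours training. With 22 children per arm, a one-sided loss also costs precision on all eight primary outcomes.

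**Working it through.** **Inputs from the protocol.** Schedule 16 weeks, three times per week (Intervention groups). Limit of three absences (Exclusion criteria). Arms of 22 and 22 (Protocol summary). Controls have no sessions (Intervention groups). The only stated figure to reproduce is the total: 22 + 22 = 44, which agrees. No alpha, power, effect size or SD is given for it, so it cannot be checked further.

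**Inputs assumed.** Attendance rate, clustering of absences within children, correlation of attendance tendency with outcome, two-sided alpha 0.05 and, for precision, 80% power. None is in the protocol, so ranges are shown.

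**1. Strictness.** 16 x 3 = 48 sessions. This takes the stated frequency, which follows the words on aerobic training, as the count of all sessions. Staying in needs at least 48 - 3 = 45, and 45/48 = 93.75%. A child attending 44/48 = 91.7% is excluded.

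**2. Share of the training arm excluded.** P(X >= 4), where X is the number of absences in 48 sessions. X is beta-binomial with mean absence rate m and intraclass correlation rho; the parameters are a = m(1 - rho)/rho and b = (1 - m)(1 - rho)/rho.

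| Mean attendance | rho 0.05 | rho 0.10 | rho 0.20 | Expected of 22 |
|---|---|---|---|---|
| 97% | 13.4% | 13.9% | 12.3% | 2.7 to 3.1 |
| 95% | 25.4% | 23.9% | 20.4% | 4.5 to 5.6 |
| 90% | 55.5% | 48.2% | 39.1% | 8.6 to 12.2 |

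Expected control exclusions are 0 in every row.

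**3. Spurious difference with no true effect.** Treat exclusion as removing the lowest fraction q on attendance tendency, which correlates r with the outcome. The retained mean shifts by r x phi(c)/(1 - q) SD, where c is the q-quantile of the standard normal.

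- q = 0.22: c = -0.772, phi(c) = 0.296, and 0.296/0.78 = 0.380.
- q = 0.50: c = 0, phi(c) = 0.399, and 0.399/0.50 = 0.798.

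Type I error comes from the noncentral t distribution with noncentrality shift/sqrt(1/22 + 1/n), where n is the number of trained children kept. Unit SD is taken in both arms.

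- 17 v 22: sqrt(1/22 + 1/17) = 0.323, 37 degrees of freedom.
- 11 v 22: sqrt(1/22 + 1/11) = 0.369, 31 degrees of freedom.

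| r | Shift, 22% dropped | Type I error | Shift, 50% dropped | Type I error |
|---|---|---|---|---|
| 0.1 | 0.04 SD | 5.2% | 0.08 SD | 5.5% |
| 0.3 | 0.11 SD | 6.4% | 0.24 SD | 9.6% |
| 0.5 | 0.19 SD | 8.8% | 0.40 SD | 18.2% |

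Chance absences blur the selection on tendency, so for a given r these shifts lean towards the high side.

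**4. Precision.** The detectable difference is (1.960 + 0.842) x sqrt(1/22 + 1/n). It is 0.845 SD with n = 22, 0.890 SD with n = 18 and 1.035 SD with n = 11.

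**The case against.** **Removal from the analysis is not stated.** A child with four absences might be withdrawn from training, not post-tested, replaced, or left out of the analysis. Analysis sets commonly belong to a statistical analysis plan, which is not shown here. This stands as a limit on wording: loss, bias and a shortfall below 22 must be put conditionally. It does not remove the point. Leaving the trial is the plain meaning of an exclusion criterion, the rule is fixed in this document, and nothing else in it restores the excluded children.

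**The loss could be small.** This also stands. At 97% attendance about three children are lost, and at a correlation of 0.1 the type I error hardly moves.

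**A reader might infer that the rule removes most of the arm.** If every child had the same 90% chance of attending each session independently, the share excluded would be 72%, or about 16 of 22. That figure should not be used to size the bias. In that model children do not differ in attendance tendency, so exclusion is chance and creates no selection through child-level traits. Bias requires children to differ, and with clustering the loss at 90% attendance is 39-56%.

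**A reader might also infer that every primary outcome is biased towards training.** The argument covers HbA1c, fasting glucose, hs-CRP and quality of life. No direction is established for IL-1B, IGF-1, growth hormone, cortisol or the blood count.

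**Conclusion.** The structural defect holds and depends on none of the assumed numbers: the sole exclusion criterion is a post-randomisation event that can occur in one arm only. Followed as written, it replaces the randomised comparison with one open to selection bias.

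The size is conditional. A loss of about a fifth to a quarter of the training arm at 95% attendance is a reasonable working figure. At a correlation of 0.3, type I error would be 6.4% with 22% dropped and 9.6% with 50% dropped. The 18.2% figure needs both half the arm lost and a correlation of 0.5, and should not be quoted alone.

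The protocol does not support saying that the trial will lose a given number of children, that it has failed to deliver 22 v 22, or that the bias favours training on all outcomes. Because the rule touches every outcome in a small, unblinded trial, it should be corrected before any result is interpreted.

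**What to change.** 1. Remove the attendance rule as an exclusion criterion, in both the Protocol summary and the Exclusion criteria entry.
2. Make the primary analysis all randomised children in the arm drawn, whatever their attendance.
3. Obtain end-of-intervention measurements from poor attenders where still possible. Otherwise use all available data, report by arm how many children met the rule or lack outcomes, and address the missing outcomes in the analysis.
4. Report sessions attended, out of 48 if that count is confirmed, as an adherence measure.
5. Label any analysis limited to three or fewer absences as supplementary and per-protocol.

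**Cost.** The text change is small. The follow-up may not be: registration is retrospective (2019-07-26), recruitment is marked complete with an expected end of 2019-07-22, and the actual dates are empty, so some post-tests may no longer be obtainable. The estimated effect may also be smaller than among full adherers.

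### The only exclusion criterion, missed training sessions, acts after randomisation and can apply only to the training arm; if excluded children are left out of the comparison, it is no longer randomised

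*Protocol*

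**What the plan says.** The Exclusion criteria section contains one item, "More than three session absence from the training", and the Protocol summary repeats it as the sole entry: "Exclusion criteria: more than three session absence from the training". Children are allocated by drawing coloured balls from a box, giving "22 people in experimental and 22 people in control group".

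Under Intervention groups, the training arm's schedule is "Aerobic training: sixteen weeks, three times per week", together with Pilates and body-weight work for which no separate frequency is given. The other arm is "Control group: Without intervention". Every primary and secondary outcome is measured "Before and after the end of interventions".

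No attendance or compliance rule is stated for controls. The protocol does not say whether a child who meets the criterion is still measured at the end or kept in the analysis.

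**The concern.** An exclusion criterion should be decidable before allocation and should apply equally to both arms. This one does neither. It depends on behaviour during the sixteen weeks after the draw, and a control child has nothing to be absent from.

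The reason for absence plays no part in the rule. A child who misses four sessions through illness, school, travel or inability to train meets it; a control in the same circumstances does not. Some of those reasons could plausibly be linked to HbA1c, fasting glucose, hs-CRP or cortisol, all of which are primary outcomes. Removing such children from one arm only could bias all eight primary and four secondary comparisons. Adjusting for baseline would deal with differences already present at the start, but not with those that arise during follow-up, such as intercurrent illness. The rule also shrinks one arm of a small trial.

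**Working it through.** **Threshold.** Intervention groups gives "sixteen weeks, three times per week". Taking that as the frequency of the whole combined programme (an assumption, since the phrase is attached to the aerobic part), there are 16 × 3 = 48 sessions. More than three absences means four or more. A child therefore stays with at least 45/48 = 93.75% attended and is excluded with 44/48 = 91.7% or less.

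**Number excluded.** The protocol gives no attendance figures, so mean absence p per session is assumed to be 2%, 5% or 10%. Selection bias requires children to differ in their tendency to be absent, so absences are taken as clustered within child: a beta-binomial with 48 trials and assumed intra-child correlation ρ = 0.1, with parameters a = p(1/ρ − 1) = 9p and b = 9(1 − p). The excluded fraction is f = P(X ≥ 4), the expected number excluded is 22f, and 22(1 − f) children are retained. Removals from the control arm are zero throughout.

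**Bias.** Let D be the gap in outcome between excluded and retained children, after any baseline adjustment, assumed to be 0.25 to 0.5 SD in either direction. With no training effect, the retained trained mean differs from the full-arm mean by f × D. The rejection rate is that of a two-sided 0.05 t-test with 22(1 − f) against 22 children and a true difference of f × D.

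**Power.** The protocol states no design effect size, so the reference is the difference that gives 80.0% power at 22 v 22, which is 0.865 SD. The row for power under exclusion uses the same difference with 22(1 − f) v 22; the standard errors are 0.309, 0.324 and 0.365 SD, against 0.302 SD at 22 v 22.

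| Mean absence | 2% | 5% | 10% |
|---|---|---|---|
| f | 0.090 | 0.239 | 0.481 |
| Excluded of 22 | 2.0 | 5.3 | 10.6 |
| Shift, D = 0.25 SD | 0.02 | 0.06 | 0.12 |
| Shift, D = 0.5 SD | 0.045 | 0.12 | 0.24 |
| Rejection rate with no effect, D = 0.25 | 5.1% | 5.4% | 6.2% |
| Rejection rate with no effect, D = 0.5 | 5.2% | 6.5% | 9.8% |
| Power for 0.865 SD under exclusion | 78% | 74% | 63% |

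**Analysis as assigned, same model.** If children over the limit gain a share g of the full effect, the as-assigned difference is 1 − f(1 − g) times the full effect, tested at 22 v 22.

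| Mean absence | 2% | 5% | 10% |
|---|---|---|---|
| g = 0.9: multiple of full effect | 0.99 | 0.98 | 0.95 |
| g = 0.9: power | 79% | 78% | 76% |
| g = 0.5: multiple of full effect | 0.96 | 0.88 | 0.76 |
| g = 0.5: power | 76% | 69% | 57% |

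**The case against.** **The analysis set may be defined elsewhere.** The statistical analysis plan is not shown, and it could keep every randomised child in the main comparison. A reader might infer from the criterion that the trial's results actually leave these children out. The protocol does not establish that: it describes no analysis set and no handling of withdrawn children. What stands is that the protocol itself fixes a one-sided rule whose ordinary meaning is that the child leaves. An analysis plan can decide whom to analyse, but it cannot supply a final blood sample that was not taken because a child had been excluded.

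**The size is assumed.** Absence rates, clustering, the gap D and the share g have no source in the protocol. That is correct, and at 2% absence the effect is negligible. At 5% it is modest.

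**Larger figures are tempting.** With independent absences at one common rate of 10%, the binomial gives 72% excluded (15.8 of 22) and power of 45%, and applying the same D gives rejection rates of 6.7 to 11.9%. Those bias figures are not coherent: if every child has the same absence rate, crossing the threshold is chance, so there is no prognostic gap to apply unless missing sessions itself alters the outcome. The clustered model is the appropriate basis, and it gives smaller values at 10%.

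**Exclusion is not always the less powerful choice.** If children over the limit gain only half the effect, analysis as assigned has lower power than exclusion (76%, 69%, 57% against 78%, 74%, 63%). This stands as a cost, but it does not restore the randomised comparison.

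**It is late.** The record is retrospective and its status is "Recruitment complete". Some final measurements may be unrecoverable. The choice of main analysis and the reporting can still be put right.

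**Conclusion.** The point holds for the rule as written: it acts after allocation, can bind only the training arm, and breaks the randomised comparison if excluded children are omitted. The first two parts follow directly from the text. The third is conditional, because the protocol does not say how excluded children are analysed.

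The size depends on attendance, ranging from negligible at 2% absence to a shift of up to 0.24 SD, with nearly double the nominal rejection rate, at 10%. A reader might also infer that the rule flatters training; the direction cannot be determined from the document. The threshold of 44 of 48 depends on the stated frequency covering the whole programme. This should be changed, but nothing here shows that the trial's conclusions are invalid.

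**What to change.** Reclassify more than three absences as non-adherence and remove it from the exclusion criteria. State that the main comparison analyses every child in the assigned arm, using every final measurement that was or still can be taken. Report how many trained children exceeded three absences and why, and report by arm any child without a final measurement. An analysis limited to adherent children may be added if it is labelled supplementary. For any further enrolment, a requirement about fitness to train belongs before the draw and should be identical for both arms.

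The cost is a few extra measurements and some dilution of the estimate. If children over the limit gain 90% of the effect, power is better than under exclusion; if they gain half, it is somewhat worse, as shown above. With recruitment complete, the dependable part of the change is the as-assigned analysis of all children who have a final measurement.

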**Secondary Ids**

empty

**Ethics committees**

**1**

Ethics committee

**Name of ethics committee**

Ethics Committee of Islamic Azad University Rasht Branch

**Postal code**

[name]

Approval date

2019-07-19, 1398/04/28

Ethics committee reference number

IR.IAU.RASHT.REC.1398.011

**2**

Ethics committee

**Name of ethics committee**

Ethics Committee of Islamic Azad University Rasht Branch

**Postal code**

[name]

Approval date

2017-09-19, 1396/06/28

Ethics committee reference number

IR.IAU.RASHT.REC.1396.168

**Health conditions studied**

**1**

Description of health condition studied

Type 1 diabetes

ICD-10 code

E10

ICD-10 code description

Type 1 diabetes mellitus

**Primary outcomes**

**1**

Description

IL-1B

Timepoint

Before and after the end of interventions

Method of measurement

using ELISA Kit

**2**

Description

High-sensitivity C-reactive Protein (hs-CRP)

Timepoint

Before and after the end of interventions

Method of measurement

using ELISA Kit

**3**

Description

IGF-1

Timepoint

Before and after the end of interventions

Method of measurement

using ELISA Kit

**4**

Description

Growth hormone

Timepoint

Before and after the end of interventions

Method of measurement

using ELISA Kit

**5**

Description

Cortisol

Timepoint

Before and after the end of interventions

Method of measurement

using ELISA Kit

**6**

Description

HbA1c

Timepoint

Before and after the end of interventions

Method of measurement

using ELISA Kit

**7**

Description

Fast blood sugar

Timepoint

Before and after the end of interventions

Method of measurement

using ELISA Kit

**8**

Description

Complete Blood Count (CBC)

Timepoint

Before and after the end of interventions

Method of measurement

using ELISA Kit

**Secondary outcomes**

**1**

Description

Quality of Life

Timepoint

Before and after the end of interventions

Method of measurement

Using questionnaire

**2**

Description

Body composition

Timepoint

Before and after the end of interventions

Method of measurement

Using weight, body mass index, waist to hip ratio and fat percent

**3**

Description

Physical fitness

Timepoint

Before and after the end of interventions

Method of measurement

Using measurement of aerobic power ,anaerobic , balance ,Flexibility and hand grip

**4**

Description

Blood pressure

Timepoint

Before and after the end of interventions

Method of measurement

Using the blood pressure device

**Intervention groups**

**1**

Description

Intervention group: Combined training group. Aerobic training: sixteen weeks, three times per week . Aerobic exercises were performed with an intensity of 50-75% of maximum heart rate ,pilates exercises, 3 set, 6-12 repeat and training using body weight with 20 minuets.

Category

Lifestyle

**2**

Description

Control group: Without intervention

Category

Lifestyle

**Email**

[contact]

Grant name

Grant code / Reference number

Is the source of funding the same sponsor organization/entity?

Yes

Title of funding source

Islamic Azad University

Proportion provided by this source

100

Public or private sector

Private

Domestic or foreign origin

Domestic

Category of foreign source of funding

*empty*

Country of origin

Type of organization providing the funding

Academic

